**Specific Aims:**

Describe the specific objectives of the proposed study. State the specific parameters, gender aspects, biological functions, rates, and processes that will be assessed by specific methods.

**Primary objectives:**

To compare the efficacy of two doses of injectable Amoxicillin plus single dose injectable Gentamicin compared to four doses of injectable Ampicillin plus single dose injectable Gentamicin in management of children hospitalized with WHO pneumonia.

**Secondary objectives:**

To compare time to resolution of danger signs of pneumonia, length of hospital stay, mortality rate, rate of complication requiring mechanical ventilation, and rate of multiorgan or renal or cardiac failure between the two treatment groups.

**Primary Outcome:** Treatment failure which is defined by the persistence of danger signs of severe pneumonia for >48 hours or deterioration within 24 hours of initiation of therapy (development of new danger signs or clinical signs of respiratory failure, or development of severe sepsis/meningitis, or, radiological deterioration).

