### **Study Interventions:**

Children between 2 months to 59 months with severe pneumonia will be studied to evaluate the proportions of treatment failure in two different arms.

We will use sealed envelopes to randomly assign the children to either treatment arms. In first arm children will receive 2 daily doses of parenteral Amoxicillin and single daily dose of parenteral Gentamicin; and in 2nd arm, children will receive 4 daily doses of parenteral Ampicillin and single daily dose of parenteral Gentamicin. After 72 hours of treatment, injection Amoxicillin and injection Ampicillin will be replaced with oral Amoxicillin but injection gentamicin will be continued for total 5 days in once daily dose. During this time patient will be suggested to discharge from hospital and attend to Ambulatory care unit for getting once daily dose of injection Gentamicin. Both the treatment arm will continue for 5 days.

During the study period, children in both study arms will also receive standardized hospital management for diarrhoea and malnutrition (*Annex 2,3*).

“Treatment failure” will be standardized, based on clinical and monitoring data. Treatment failure is defined by the persistence of danger signs of severe pneumonia for >48 hours or deterioration within 24 hours of initiation of therapy or if child needs mechanical ventilation, dies at any time during hospital stay or left the hospital against medical advice.

During the study period any child from either study group who develops the features of “clinical failure” (any two of three criteria in the definition below) will be managed according to best practice in the clinical context. If children fail any arm of treatment, they should be rescued with second line antibiotic regimen, which is injection ceftriaxone and injection levofloxacin. Hypoxia will be managed by B-CPAP or humidified high flow air / O2 mix at 2 l/kg/min through nasal cannula.

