### **Laboratory investigations:**

No additional laboratory investigations will be required to perform this study. Routine management of severe pneumonia will be followed as per the existing pneumonia guideline practiced in Dhaka Hospital. The patients with suspected sepsis will be investigated for source of infection by CBC, Blood culture and chest X-ray. Any patient with severe acute malnutrition (SAM) and cough and/or fast breathing will be investigated for chest X ray and CBC. There will be no incurrence of hospitalization cost to conduct the research.

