## Data Safety Monitoring Plan (DSMP)

All clinical investigations (biomedical and behavioural intervention research protocols) should include the Data and Safety Monitoring Plan (DSMP) to provide the overall framework for the research protocol's data and safety monitoring. It is not necessary that the DSMP covers all possible aspects of each element. When designing an appropriate DSMP, the following should be kept in mind.

- a) All investigations require monitoring;
- b) The benefits of the investigation should outweigh the risks;
- c) The monitoring plan should commensurate with risk; and
- d) Monitoring should be with the size and complexity of the investigation.

Safety monitoring is defined as any process during clinical trials that involves the review of accumulated outcome data for groups of patients to determine if any treatment procedure practiced should be altered or not

Data safety Monitoring will be rigorously performed throughout the course of the study mainly by an independent DSMB who will visit randomly to review the forms for completeness, legibility, and internal consistency. icddr,b's ERC required reporting of all serious adverse events (SAE) within 24 hours; for this study all adverse events (AE) will also be reported by the study investigators to the DSMB within 24 hours of their occurrences using a standard case reporting form. As this is an open trial the implications of an adverse event can be better interpreted throughout the conduct of the trial than would be possible if any blinding was

involved. The DSMB will have full access to all case reporting forms and trial data, not only every 6 months, but whenever it is appropriate if there are any concerns over excess adverse events or unbalanced events between the three study groups. All aspects of intervention and interpretation will be performed according to rigorously standardized standards of procedures (SOPs).

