**139. Gastric lavage for CS :**

1= +ve for MTB, 2= +ve for non-tubercular mycobacteria, ☐  
3= no growth of mycobacteria, 4= could not be sent

140. **Chest x-ray :** 1. lobar consolidation, 2. patchy consolidation, 3=discrete opacities  
4. Normal x-Ray ☐

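### Radiological deterioration counts alone as a primary failure in two of the protocol's definitions, but no repeat film is scheduled, the trial is open label, and the case record form cannot record a change between films

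*Protocol*

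**What the plan says.** The Primary Outcome appears with the same wording under Specific Aims and under Sample size calculation. One limb is "deterioration within 24 hours of initiation of therapy (development of new danger signs or clinical signs of respiratory failure", and the list continues "or development of severe sepsis/meningitis, or, radiological deterioration". The items are joined by 'or', so each is sufficient alone.

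Treatment failure is also defined in the Project Summary and under Study Interventions. There the limb reads "deterioration within 24 hours of initiation of therapy or if child needs mechanical ventilation, dies at any time during hospital stay", followed by leaving against medical advice. Neither version mentions imaging, and Study Interventions says failure "will be standardized, based on clinical and monitoring data". The Intention to treat section refers back to failure as defined in the proposal without saying which definition it means.

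On films, Laboratory investigations states "No additional laboratory investigations will be required to perform this study" and defers to the hospital's existing pneumonia guideline. It names two groups for chest X-ray. The first is suspected sepsis: "The patients with suspected sepsis will be investigated for source of infection by CBC, Blood culture and chest X-ray". The second is any child with severe acute malnutrition (SAM) plus cough and/or fast breathing. The section on the respiratory ward leaves further tests to clinical indication.

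In the case record form (CRF, Annex 4), item 140 is a single chest X-ray entry coded "1. lobar consolidation, 2. patchy consolidation, 3=discrete opacities" or normal. The Data Safety Monitoring Plan confirms the lack of blinding: "As this is an open trial".

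**The concern.** Deterioration on a film is a change, so it needs two comparable films, the second early enough to fall within 24 hours of starting treatment. The protocol schedules no such pair, states no criterion for worsening and names no reader. Whether a child can fail on this item therefore depends on whether someone who knows the allocation orders a second film.

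Fewer repeat films in the amoxicillin arm would lower its failure count and favour non-inferiority; more would count against it. Neither shift would reflect the drugs. A film-only failure also could not be traced afterwards, because the CRF has no place to record it.

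**Working it through.** **1. The definitions side by side**

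| Place in protocol | Radiological item? | Ventilation, death, leaving against advice? |
|---|---|---|
| Project Summary, Treatment failure | No | Yes |
| Specific Aims, Primary Outcome | Yes, sufficient alone | No |
| Study Interventions | No; clinical and monitoring data | Yes |
| Sample size calculation, Primary Outcome | Yes, sufficient alone | No |
| Intention to treat analysis | Refers back to the proposal's definition | Yes |

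The protocol therefore disagrees with itself on whether a film belongs in the endpoint at all.

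**2. Can the item be recorded?** CRF item 140 holds one result, with no date, no second film and no code for worsening. The D1, D2 and D3 examination sheets have no X-ray item. Item 153 records treatment failure without its component. Change between two films cannot be entered or audited.

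**3. The plan's own sample size.** Inputs from Sample size calculation: failure proportion 0.50 in both arms, margin 0.16, one-sided alpha 0.025, power 0.80.

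n per arm = 2 × 0.50 × 0.50 × (1.960 + 0.842)² / 0.16² = 153.3, rounded up to 154, or 308 in total. This matches the protocol. Power at 154 per arm is 80.2%.

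**4. Effect of uneven detection.** Let b be the net between-arm difference in film-only failures. The documents give no value for b, so the range below is assumed. With n = 154 per arm and SE = √[(pC(1−pC) + pT(1−pT)) / n], the probability of declaring non-inferiority is Φ[(0.16 − (pT − pC)) / SE − 1.960].

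- Excess on amoxicillin, no true difference: pC = 0.50, pT = 0.50 + b. This gives power.
- Deficit on amoxicillin, true difference at the margin: pC = 0.50, pT = 0.66 − b. This gives type I error.

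Worked case, b = 0.03. For power, SE = √[(0.25 + 0.53 × 0.47)/154] = 0.0569; 0.13/0.0569 − 1.960 = 0.32; Φ = 62.7%. For type I error, SE = √[(0.25 + 0.63 × 0.37)/154] = 0.0560; 0.03/0.0560 − 1.960 = −1.42; Φ = 7.7%.

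| b (points) | Children of 154 | Power, excess on amoxicillin | One-sided type I error, deficit on amoxicillin |
|---|---|---|---|
| 0 | 0 | 80.2% | 2.5% |
| 1 | 1.5 | 75.0% | 3.8% |
| 2 | 3.1 | 69.1% | 5.5% |
| 3 | 4.6 | 62.7% | 7.7% |

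**5. What would produce such a b?** As an illustration with assumed rates, suppose repeat films are taken in 20% versus 10% of children and 30% of them are read as worse. The raw gap is 0.20 × 0.30 − 0.10 × 0.30 = 0.03. Children who already fail on another criterion must be removed. At the protocol's 0.50 failure proportion, and if film findings were independent of other failure, the film-only gap is 0.03 × 0.50 = 0.015, or 1.5 points; 0.015/0.16 is about 9% of the margin. Positive correlation makes it smaller.

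**The case against.** Three stronger readings are tempting, and the documents do not support them.

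- A reader might infer that films are taken only on clinical suspicion. SAM with cough and/or fast breathing triggers a film by rule. That rule does not provide a repeat film, so the second film remains discretionary.
- A reader might infer that X-ray ordering drives the primary outcome. The item is one of several, limited to the first 24 hours, and its frequency is not given. Children filmed again that early may often have failed already on new danger signs, respiratory failure or severe sepsis.
- A reader might infer that many children will have no baseline film. The hospital guideline is not shown, and item 140 lacks the not-done code that blood culture has, which hints that a film was expected in every child. This does not supply a second, dated film.

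Other components, such as lethargy, are also open to unblinded judgement, and the protocol promises standardised assessment and operating procedures that are not shown. That is fair. The film item differs in that it needs an optional test to exist at all, and the CRF cannot hold its result.

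It can also be said that this is part of a wider conflict between definitions. That stands and shapes the remedy: editing only the two Primary Outcome statements would leave ventilation, death and leaving against advice unreconciled.

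**Conclusion.** The point holds in a limited form. Two of the protocol's definitions let a film alone decide primary failure, two leave films out, and the trial as described can neither ascertain the item evenly nor verify it. The possible bias runs in either direction and is zero if repeat filming and reading do not differ by arm.

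The size is unknown. Over an assumed net difference of 1 to 3 points, power falls from 80% to about 75%–63%, or one-sided type I error rises from 2.5% to about 4%–8%. These figures rest on the protocol's 0.50 failure proportion, its 0.16 margin, 154 children per arm and an unpooled normal approximation. Even without bias, a film-only failure could not be audited from the CRF. The change is worth making because it costs almost nothing, not because a large distortion has been shown.

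**What to change.** Reconcile the failure definitions in the Project Summary, Specific Aims, Study Interventions, Sample size calculation and Intention to treat sections into one analysed primary endpoint. In doing so:

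- Remove radiological deterioration as a criterion of that endpoint. Counting it only alongside another listed failure sign amounts to the same thing, since that sign already suffices.
- Report film findings descriptively by arm, with the number of children filmed.
- Settle in the same edit whether ventilation, death and leaving against advice belong in the endpoint.
- Order no extra films.
- State that the edit changes only the endpoint used for analysis and not the clinical management of any child. This sentence is needed because Study Interventions links failing an arm to rescue treatment.

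The cost is protocol wording. The downside is that a few film-only deteriorations, which the CRF could not document anyway, no longer count. The sample size need not change for this point unless the assumed 0.50 failure proportion is revised.

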**Secondary outcomes:**

1. Time to resolution of danger signs of severe pneumonia
2. Length of hospital stay
3. Death during hospitalization

### **Background of the Project including Preliminary Observations:**

Provide scientific validity of the hypothesis based on background information of the proposed study and discuss previous works on the research topic, including information on sex, gender and diversity (ethnicity, SES) by citing specific references. Critically analyze available knowledge and discuss the questions and gaps in the knowledge that need to be filled to achieve the proposed aims. If there is no sufficient information on the subject, indicate the need to develop new knowledge.

The World Health Organization (WHO) estimates there are 156 million cases of pneumonia each year in children younger than five years, with as many as 20 million cases severe enough to require hospital admission [1]. In the developed world, the annual incidence of pneumonia is estimated to be 33 per 10,000 in children younger than five years and 14.5 per 10,000 in children 0 to 16 years [2]. Approximately one-half of children younger than five years of age with community-acquired pneumonia (CAP) require hospitalization [3]. In developing countries, respiratory tract infections are not only more prevalent but more severe, accounting for more than 2 million deaths annually; pneumonia is the number one killer of children in these societies [1 4]. Recent study from Dhaka hospital reported a visit of 225 children with severe pneumonia and hypoxemia from 2011 to 2013[5].

The 2008 WHO guidelines for treatment of non severe pneumonia (cough, fever and fast breathing) recommend health workers to provide oral antibiotics for three days at home but urgent referral for hospitalization for parenteral (injectable) antibiotics and other supportive therapy after administration of first dose of antibiotics, if the child has severe pneumonia (cough, fever, fast breathing and lower chest indrawing) or very severe disease (pneumonia with the presence of WHO defined danger signs) [6]. Often inability to access a referral facility deprives these children from getting appropriate care. For many families, seeking treatment for their children at a health care facility is often logistically and financially burdensome thus denying them early administration of antibiotics within 48 h that can potentially improve their outcomes [7]. Additionally transport to a distant facility can entail serious delays in effective treatment. Many children with severe pneumonia referred for admission to a hospital could die in transit or reach too sick to be saved [7]. In addition, when hospitalized, the children with severe pneumonia are vulnerable to nosocomial infections in crowded hospital wards and are also at risk of needle-borne infections due to parenteral therapy. Two important studies have addressed such barriers to the recommended treatment of severe pneumonia. The first study was intended to determine whether oral antibiotics are equivalent to injectable antibiotics when both are given in the hospital. This was an open label equivalency study called APPIS (Amoxicillin Penicillin Pneumonia International Study), which was a large multicentre randomized controlled trial comparing injectable penicillin versus oral amoxicillin given for 7 days to children in the hospital [8]. The second study was called “NOSHOTS” (New Outpatient Short-Course Home Oral Therapy for Severe Pneumonia Study) and was a randomized, open-label equivalency trial done at seven study sites in Pakistan and compared initial hospitalization and parenteral ampicillin for 48 h followed by 3 days of oral amoxicillin at home, to 5 days of home-based treatment with oral amoxicillin [9]. NO-SHOTS showed that home treatment with high-dose oral amoxicillin is equivalent to hospital based treatment with parenteral ampicillin in selected children aged 3–59 months with WHO defined severe pneumonia [9]. Later, another study- the MASS study (Multicenter Amoxicillin Severe pneumonia Study) showed that clinical treatment failure and adverse event rates among children with severe pneumonia treated at home with oral amoxicillin did not substantially differ across geographic areas (Bangladesh, Ghana, Vietnam and Egypt) and hence home-based therapy of severe pneumonia could possibly be applied to a wide variety of settings [10]. Thus oral amoxicillin at home has proven clinically efficacious in various settings across the world for treatment of selected children with WHO defined severe pneumonia. The Lancet Series on Childhood Pneumonia and Diarrhoea has reported that case management is one of the three most effective interventions to reduce pneumonia deaths in children but also noted that the cost effectiveness of these interventions in national health systems needs urgent assessment [11].

#### Antimicrobial selection:

*Streptococcus pneumoniae* is the main pathogen that causes community-acquired pneumonia worldwide, in children under five years (30%-50%) and *Haemophilus influenza* (10%-30%). Other frequent causes include *Mycoplasma Chlamydia* and *Legionella* species [12]. Resistance of *S pneumoniae* to penicillin and macrolides has been nearly stable in recent years [13]. The introduction of the conjugated pneumococcal vaccine in children has decreased the incidence of invasive penicillin-resistant cases; however, infections with serotypes not affected by the vaccine have increased. Amoxicillin is active against most *S pneumoniae* and *H influenza* strains and better absorbed than ampicillin and thus been widely used for treating respiratory infections (including pneumonia) in children [14]. According to WHO pneumonia guideline, children with fast breathing should be treated with Amoxicillin orally at a dosage of 40mg/kg/dose twice daily for five days [15]. In addition children aged 2-59 months with severe pneumonia should be treated with parenteral ampicillin (or penicillin) 100mg/kg/dose 6 hourly and gentamicin 7.5 mg/kg/dose once daily for 3-5 days as a first-line treatment [15].

#### Antimicrobial properties:

Amoxicillin, an acid stable semi synthetic penicillin shown to be effective against a wide range of infections when given orally and available for intramuscular and intravenous injection. Amoxicillin has an antimicrobial spectrum and level of activity essentially the same as for ampicillin [16]. Amoxicillin has been shown to have more rapid and complete bactericidal action than ampicillin against *E.coli* in vitro. Amoxicillin is active at low concentrations against *Staphylococcus aureus* and *epidermidis*, *Streptococcus pyogenes*, *Diplococcus pneumoniae* and *Streptococcus viridians* and many strains of *Streptococcus faecalis*. A combination of amoxicillin and an aminoglycoside is synergistic against *Streptococcus* species which are the main pathogens causing childhood pneumonia [16].

#### Pharmacokinetics:

Peak plasma concentrations and the plasma level profile after intramuscular injection of amoxicillin are dose-related and similar to that after oral administration of an equivalent dosage. Bioavailability is also similar after oral or intramuscular administration. The peak plasma concentration after intravenous injection varies according to the rapidity of the injection but when given by bolus injection (over 3 to 30 seconds) it is 6 to 12 times that attained after the same dose given intramuscularly. A plasma concentration of 5µg/ml is exceeded for about 3 hours after intramuscular and 1 hour after intravenous injection of 500mg amoxicillin, in patients with normal renal function.

#### Therapeutic Trials:

Although the efficacy of oral amoxicillin for several infections in children is well documented, there are relatively few papers on its parenteral use. Nevertheless, published and unpublished data available suggest that amoxicillin administered by the intramuscular and intravenous routes is effective in infections of the urinary and respiratory tracts, and in meningitis and septicaemia caused by a variety of susceptible organisms. Parenteral amoxicillin has been successful in eradicating the original pathogen in about 85% of urinary tract infections caused by Gram-positive or Gram-negative bacteria including those in patients with underlying urinary tract abnormalities in children. At a dosage of 500mg 8-hourly, intramuscular or intravenous amoxicillin has achieved clinical and/or bacteriological responses in 87 to 100% of patients with bronchopneumonia, acute bronchitis or exacerbations of chronic bronchitis although many cases were not proven to be of bacterial origin.

Moreover the injectable amoxicillin is cost effective compare to injection ampicillin. Less manpower is required to administer amoxicillin compared to ampicillin. Both the above facts contributed to less incidence of nosocomial infection. There is not enough research to support this data but our anecdotal observation suggests that the present therapy will have better compliance as you are switching over to oral form.

With the above given facts our aim of conducting this study is to evaluate the efficacy of two doses of parenteral Amoxicillin plus single dose Gentamicin compared to four doses of parenteral Ampicillin plus single dose Gentamicin in managing children under five with severe pneumonia.

